#### Sample size calculation

In the athletes population, all swimmers under competition in the Porto's team Swimmers will be eligible to the study, a population of 40 participants in total can be evaluated for this study purposes. Using previous studies comparing the rate number of respiratory infections for this specific population, elite swimmers under 12 weeks high intensity period before competitions 40% have a respiratory infection, with an alpha of 0,05 the power will be 35%.

### **4.3.3. Acute exercise and meal challenge (IV)**

In the randomized cross-over study, includes all randomized subjects which took at least one meal challenge and exercise intervention and who had at least one post-baseline immune marker variable measurement. Primary and secondary endpoints will be analyzed for the presence of a carry-over effect in the meal challenge study [69].

Changes in the immune biomarkers and endocrine will be presented as mean  $\pm$  standard deviation. Data obtained from high fat and low fat meal challenge will be compared using paired t-tests. Repeated-measures analysis of variance (ANOVA) were used to analyze the effects of the challenges.

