#### **4.1.4. Effect of an high fat meal on neuro-immune-endocrine response to an acute exercise challenge (IV)**

This is a randomized cross-over trial, with a wash out period of 7 days, single-blinded, placebo controlled. Study design is specified in figure 1. Participants will be recruited from advertisement and four different groups will be compared: obese-asthmatic; asthmatic non-obese; obese without asthma and non-asthmatic and non-obese. Stratification will be done accordingly to having asthma and  $BMI \geq 30 \text{ kg/m}^2$ . All patients will be allocated to a meal challenge in which a high fat meal will be followed by a low fat meal or vice-versa, meal challenge order will be randomized and participants blinded to the intervention. Three hours after it will be followed by an exercise challenge, which is aimed to induce acute immune changes. The main outcome will be exercise-immune function (immune function markers) changes after a diet challenge. As secondary outcomes stress/inflammatory markers, endocrine mediators, as well as blood fatty acids will be measured. Lung function,  $VO_2$  and airway inflammation will be assessed by exhaled breath condensate inflammatory markers and eNO. Any adverse events of the challenge will be registered, namely respiratory infections, gastro-intestinal symptoms and muscular ache.

[figure not shown]

**Figure1.** Randomized cross-over study trial, single-blinded to meal intervention. Measures (1.1; 1.2;2.1;2.2) immediately before and after exercise challenge include: Immune-endocrine-metabolomic response (blood, urine and saliva samples); Pupilometry; Lung-function and VO2 consumption; skin prick histamine reactivity

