### Randomization and blinding

Patients will be informed of the procedure but they will be blinded to which is the intervention (high fat or low fat meal). Stratified blocked randomization will be performed accordingly to being asthmatic or obese. This methodology was chosen despite acute changes are the aim, to exclude and evaluate the intervention order in the studied outcomes. Equal number of participants will be allocated to each group.

Allocation concealment will be prevailed as investigator will only know the intervention order for that participant at the moment the meal is provided. Exercise challenge and outcome assessment, namely urine, blood sample collection, exhaled breath condensate and lung function will only be performed by another investigator blinded to the meal order.

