#### Sample size calculation

This study is a 2-intervention, 2-period cross over design. Each subject received each meal once in one of the two periods in an order dependent on the randomization, and consequently comparisons were made within-subject. Estimates of between-subject variability have been derived for from previous studies evaluating meal high carbohydrate ingestion in physically active subjects, before an exercise challenge[70]. Standard-deviation was estimated for interleukin-6, more specifically to be 1.3 of standard deviation. This cannot be generalized to this population as they are not physically activ, but no study was previously performed in asthma patients or obese. Only in one previous study performed an high fat challenge in asthma and obese patients and showed a standard deviation in IL-6 of 0.5[63]. Assuming a range difference of 1, it was calculated a value over 80% power to demonstrate (at the 5% level of significance) a difference between interventions of 1 pg/ml in the IL-6, in a sample size of 25 patients in each sequence. To allow for dropouts the study was designed to recruit 30 patients in total, 15 in each group asthma and obese.

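### Study IV's paired t-tests cannot use the one-period participants in its analysis set and have no period term, and the ANOVA as written does not repair this

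*Protocol*

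**What the plan says.** Section 4.3.3, Sample size calculation, gives the design: "This study is a 2-intervention, 2-period cross over design". Section 4.1.4 sets the order of meals at random, "with a wash out period of 7 days".

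The analysis paragraph of section 4.3.3 contains four relevant statements:

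- The analysis set is "all randomized subjects which took at least one meal challenge and exercise intervention", provided they also have at least one immune marker measured after baseline.
- On carry-over: "Primary and secondary endpoints will be analyzed for the presence of a carry-over effect in the meal challenge study".
- The meal comparison: "Data obtained from high fat and low fat meal challenge will be compared using paired t-tests".
- A second method: "Repeated-measures analysis of variance (ANOVA) were used to analyze the effects of the challenges". Its factors are not listed, and its role beside the t-test is not stated.

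Section 4.1.4, Randomization and blinding, adds "Stratified blocked randomization will be performed accordingly to being asthmatic or obese". It gives the removal and assessment of any effect of meal order as the reason for this method. Section 4.1.4 also announces a comparison of four groups formed by asthma and obesity. Section 4.3.3 names no period, sequence, asthma or obesity factor. For urine metabolomics in the clinical trials, section 4.2.10 restricts analysis to those who completed the whole protocol, which is a different population again.

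**The concern.** The stated test cannot be carried out on the stated population. Someone who attends one visit is in the analysis set but contributes no within-person difference. In practice the meal comparison becomes a completers analysis, though the plan describes something wider.

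The second gap is order. Each visit includes a maximal-effort treadmill test, repeated after a week, so a difference between first and second visits is plausible whichever meal was eaten. A plain paired t-test puts that difference into its error term. If the two sequences finish with unequal numbers, part of it also goes into the meal estimate. The protocol says order is to be dealt with, but no named analysis does so. The announced four-group comparison also has no named analysis.

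**Working it through.** **Inputs from the protocol** (4.3.3, Sample size calculation): target difference 1 pg/ml in IL-6; SD 1.3 from one cited study and 0.5 from another; 5% level; power over 80% with 25 per sequence; 30 recruited in total.

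**Assumptions, not in the documents:** two-sided testing; within-person correlation ρ; period effect π (second visit minus first); numbers completing each sequence. An SD of the difference of 1.3 corresponds to a single-measurement SD of 1.3 with ρ = 0.5, because SD_diff = SD·√(2(1−ρ)).

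**The plan's own figure.** A two-group normal approximation with SD 1.3 and 25 per group gives 77.6% power, and 80% needs 27 per group. Read as a cross-over with 50 pairs, power is 96.5% at ρ = 0 and above 99.9% at ρ = 0.5. So power over 80% holds as a lower bound for the cross-over. This point does not dispute it.

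**Step 1: what a period effect does to the paired t-test.** Let n₁ complete high-fat-first and n₂ low-fat-first. The high-minus-low difference has mean δ − π in the first sequence and δ + π in the second, so

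bias = π(n₂ − n₁)/(n₁ + n₂).

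- 15/15: bias 0 for any π.
- 16/10: −6/26 × π, which is −0.06 at π = 0.25, −0.12 at 0.5 and −0.23 at 1. If π is negative the signs reverse.

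**Step 2: the error term with balanced sequences.** The expected sample variance of the differences is 1.3² + π²·30/29, but the true sampling variance uses 1.3² = 1.69 only.

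- π = 0.25: 1.69 + 0.065 = 1.755. The effective critical value is 2.045 × √(1.755/1.69) = 2.08, giving a type I error of about 4.6% on 29 df.
- π = 0.5: 1.69 + 0.259 = 1.949; critical value 2.20; about 3.6%.
- π = 1: 1.69 + 1.034 = 2.724; critical value 2.60; about 1.5% (1.4% by simulation).

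**Step 3: simulated power for 1 pg/ml, SD of the difference 1.3.** The adjusted estimate is the mean of the two sequence-specific means, with a pooled error.

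| Completers | π | Bias | Paired | Adjusted |
|---|---|---|---|---|
| 15/15 | 0.25 | 0 | 98% | 98% |
| 15/15 | 0.5 | 0 | 97% | 98% |
| 15/15 | 1 | 0 | 94% | 98% |
| 16/10 | 0.25 | −0.06 | 94% | 96% |
| 16/10 | 0.5 | −0.12 | 89% | 95–96% |
| 16/10 | 1 | −0.23 | 66–67% | 95–96% |
| 16/10 | −1 | +0.23 | 98% | 96% |

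If 0.5 is taken as the SD of the difference, paired power is at least 99.9% at 15/15, 13/11 and 16/10. The bias from Step 1 does not depend on the SD.

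**Step 4: one-period participants.** Assume 25 complete pairs plus 5 people with one period, single-measurement SD 1.3. With complete pairs only, SE = √(2 × 1.69 × (1−ρ)/25) apart from a negligible imbalance term. Generalised least squares on all 30 gives:

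| ρ | SE, pairs only | SE, all 30 | Efficiency gain |
|---|---|---|---|
| 0 | 0.368 | 0.3507 | 10% |
| 0.5 | 0.2602 | 0.2539 | 5% |
| 0.75 | 0.184 | 0.1817 | 2.5% |

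At ρ = 0 power rises from 77.6% to 81.4%.

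**Step 5: the carry-over check.** Assume it is a two-sample test on participant totals, with SD 1.3·√(2(1+r)) and r from 0.3 to 0.7. With 15 per sequence, power against a carry-over of 1 pg/ml is 20% to 24%. A non-significant result would be weak reassurance.

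**The case against.** The strongest reply is that section 4.3.3 does not stop at the paired t-test. A repeated-measures ANOVA follows, and a statistical analysis plan that is not shown may list its factors. This stands in part. A reader might infer that the plan ignores period and leaves the strata unused altogether, but the documents show this for the t-test only. Nothing shows that the ANOVA contains those terms either. A conventional repeated-measures ANOVA also needs complete cases, so it leaves the conflict with the analysis set in place.

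A reader might also infer that omitting asthma and obesity biases the pooled meal effect. It does not: within-person differences already remove the main effects of the strata. What section 4.3.3 lacks is a named meal-by-group analysis.

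A third tempting reading is that the carry-over test decides which analysis is used. The protocol states no such rule. It says only that endpoints will be examined for carry-over, and it specifies a 7-day washout with reasons. The check's low power is a limitation, not an error in the plan.

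Finally, the large power losses belong to one corner. A period effect of 1 pg/ml equals the whole target effect, and the 16/10 split is assumed. The opposite sign gives paired power above the adjusted figure, and an SD of 0.5 removes the power loss. Blocked randomisation with equal allocation makes the starting sequences nearly equal, so bias needs both a period effect and unequal completion. All of this stands and limits the size of the point.

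**Conclusion.** The point holds as a mismatch within the protocol. The analysis set admits one-period participants, the paired t-test cannot use them, and the stated intention to remove and assess order is not carried out by any analysis whose terms are given. The ANOVA, as written, does not resolve this.

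The consequences are modest unless completion is uneven. With balanced sequences the estimate is unbiased and the loss is at most about 4 points of power over the period effects considered. With 16/10 completers the estimate shifts by about 6% to 23% of the 1 pg/ml target, and the direction cannot be known in advance. Dropping 5 one-period participants of 30 forgoes about 2.5% to 10% in efficiency. These sizes rest on assumed period effects, correlations and completion splits. The documents do not support a claim that serious bias is expected. The mismatch itself needs none of these assumptions, and it is cheap to remove.

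**What to change.** In section 4.3.3, replace the paired t-test as the primary meal comparison with a linear mixed model on the analysis set already defined:

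- Fixed effects for meal and period, with the sequence term also reported, and a random participant effect.
- The pooled meal effect as the primary contrast.
- Meal-by-asthma and meal-by-obesity interactions in an exploratory extension, labelled as such, so that the announced group comparison has a named analysis.
- Either drop the repeated-measures ANOVA or state its factors and its role.
- Report the carry-over check descriptively.
- Reconcile the completers-only rule for urine in section 4.2.10 with the analysis set, or state that it is a deliberate exception.

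**Cost.** This is a change of wording, with no new data. The period term takes about one degree of freedom. If there is no period effect, power falls by up to about 1 point, or about 3 points at an extreme 17/8 split (95.9% to 93.0%). Using one-period participants relies on their missing visit being missing at random given the data observed, which should be stated. The exploratory interactions will be imprecise with about 30 participants.

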#### Sample size calculation

This study is a 2-intervention, 2-period cross over design. Each subject received each meal once in one of the two periods in an order dependent on the randomization, and consequently comparisons were made within-subject. Estimates of between-subject variability have been derived for from previous studies evaluating meal high carbohydrate ingestion in physically active subjects, before an exercise challenge[70]. Standard-deviation was estimated for interleukin-6, more specifically to be 1.3 of standard deviation. This cannot be generalized to this population as they are not physically activ, but no study was previously performed in asthma patients or obese. Only in one previous study performed an high fat challenge in asthma and obese patients and showed a standard deviation in IL-6 of 0.5[63]. Assuming a range difference of 1, it was calculated a value over 80% power to demonstrate (at the 5% level of significance) a difference between interventions of 1 pg/ml in the IL-6, in a sample size of 25 patients in each sequence. To allow for dropouts the study was designed to recruit 30 patients in total, 15 in each group asthma and obese.

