### **Methods:**

Study design: An observational study with validation methodology will be applied to evaluate respiratory infections; in prospective cohort study of 12 weeks a group of athletes under high competition levels, respiratory infections and potential risk factors accordingly to literature will be evaluated; an prospective case-control with a moderate- exercise program intervention will compare the impact in respiratory infections in elderly under exercise training or not; a randomized, placebo controlled cross-over trial will evaluate the impact of a high fat/high energy meal challenge in an acute exercise challenge; randomized clinical trial will be used to ascertain the impact of physical activity reduction in the immune function

Selection of participants: For questionnaire validation will be selected participants with respiratory infections; athletes will be selected from a high elite pre-competition level team; elderly will be selected from general population, namely from senior universities and nursing homes; asthma and obese participants will be selected from an university population sample

Sample Size: 281 patients will be chosen as target for evaluation in respiratory tract infections validation; 40 patients will be evaluated in total in swimmers illness-prone study trial; 40 participants will be selected to evaluate exercise program in the elderly; 30 participants, with a

equal number of obese, asthma, obese and asthma and a control will be allocated to the meal interventions (60 participants in total) and a target of 60 participants will be randomized to the physical inactivity intervention.

Measurements: Upper respiratory tract infections number, severity and quality of life impact, immune system markers, complete blood cell count, pro-inflammatory and anti-inflammatory mediators, namely cytokines, and metabolomic.

Main Outcomes: Respiratory Infection Risk in Susceptible Population, Immune markers parameter related with acute exercise and physical inactivity interventions (balance between pro-inflammatory and anti-inflammatory cytokines).

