### 4.3. Statistical analysis (I-V)

All statistic analyses will performed using the SPSS 20.0 software (Chicago, Ill) and Excel, Microsoft Office, for data assembly and graphical analysis. Normality of data distribution will be assessed by the Kolmogorov-Smirnov test, histogram and QQ plot distribution. Results will be expressed as median and inter-quartile range or mean and standard deviation and in discrete variables as count and percentage. If a normal distribution is described t-test-student would then be used in continuous variables. For non-normal data, non-parametric tests, namely Mann-Whitney will be used, to compare groups. Measures with discrete distributions are expressed as counts (%) and analyzed with Pearson-Chi Square or Fisher exact test. The minimum threshold for statistical significance will be  $p \leq 0.05$ . In data with skewed distributions, logarithmic transformation will be done and if appropriate (normal distribution is achieved) comparisons will be made with this change.

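### Study IV gives conflicting enrolment totals (50 implied, 30 and 60 stated), and its power calculation cannot be reconstructed from the inputs given

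*Protocol*

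**What the plan says.** Section 4.1.4 of the Protocol describes a randomized two-period cross-over in which each person eats both meals, in one of two orders. It compares four groups: obese with asthma, asthma only, obese only, and neither. Its randomization paragraph requires equal group sizes.

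The sample size section under 4.3.3 states that "it was calculated a value over 80% power to demonstrate" the target effect, namely "a difference between interventions of 1 pg/ml in the IL-6", with testing "at the 5% level of significance". On numbers it says: "in a sample size of 25 patients in each sequence. To allow for dropouts the study was designed to recruit 30 patients in total". It then splits the 30 into 15 with asthma and 15 with obesity.

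On variability it says: "Estimates of between-subject variability have been derived for from previous studies evaluating meal high carbohydrate ingestion in physically active subjects". The IL-6 value is given as "more specifically to be 1.3 of standard deviation", with a caution that it does not carry over to this less active population. A second SD, 0.5, follows, attributed to a high-fat challenge in asthma and obese patients and cited to reference 63.

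The sample size paragraph of the Summary begins with 30 participants and goes on: "equal number of obese, asthma, obese and asthma and a control will be allocated to the meal interventions (60 participants in total". The Portuguese Resumo repeats both figures.

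**The concern.** A recruitment target that allows for dropouts must exceed the number the power rests on. Here the powered number is 50 by multiplication and the target is 30, while the Summary supports 30 and 60 in one sentence. The group structure conflicts as well, with two groups of 15 in one place and four equal groups elsewhere.

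The candidate totals differ twofold, so the number of people who undergo the exercise challenge is not settled. A stratified blocked list with equal groups cannot be drawn up without one total. Because the section does not say which SD or correlation was used, nobody can tell which total the stated power belongs to.

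**Working it through.** **1. Counts**

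| Place | Total | Groups |
|---|---|---|
| 4.3.3, powered number | 2 × 25 = 50 (derived, not written) | not stated |
| 4.3.3, recruited | 30 | 2 × 15 |
| Summary and Resumo | 30 and 60 | 4 equal |
| 4.1.4 | not stated | 4 equal |

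30 / 4 = 7.5, which is not a whole number. 60 / 4 = 15.

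**2. Inputs for power**

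- From 4.3.3: difference 1 pg/ml, 5% level, SD 1.3 or 0.5, within-subject comparison. Section 4.3.3 plans paired t-tests.
- Not stated, so assumed: two-sided test (section 4.3 says only "The minimum threshold for statistical significance will be" p ≤ 0.05, with no sidedness), and within-person correlation r from 0 to 0.5.

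**3. Formula**

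SD of the within-person difference: SDd = SD × √(2(1 − r)). Power comes from the noncentral t distribution with N − 1 degrees of freedom and noncentrality 1 × √N / SDd.

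For SD 1.3:
- r = 0: SDd = 1.3 × √2 = 1.838
- r = 0.25: SDd = 1.592
- r = 0.5: SDd = 1.300

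For SD 0.5 and r = 0: SDd = 0.707.

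**4. The plan's own figure first (25 per sequence, N = 50)**

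With SD 1.3 and r = 0, noncentrality is 7.071 / 1.838 = 3.85 and power is 96.5%. So over 80% is true as a lower bound. It is not what a calculation aimed at 80% would return. At N = 50, exactly 80% corresponds to SDd = 2.47, larger than either quoted SD produces at any r of 0 or above.

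**5. Power by number of completers**

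| N completing | SD 1.3, r = 0 | SD 1.3, r = 0.25 | SD 1.3, r = 0.5 | SD 0.5, r = 0 |
|---|---|---|---|---|
| 25 | 74.2% | 85.4% | 95.8% | about 100% |
| 30 | 82.1% | 91.4% | 98.3% | about 100% |
| 50 | 96.5% | 99.2% | about 100% | about 100% |
| 60 | 98.6% | 99.8% | about 100% | about 100% |

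Total N needed for 80%: 29, 22 and 16 for SD 1.3 at r = 0, 0.25 and 0.5, and 7 for SD 0.5 at r = 0. A one-sided test at SD 1.3 and r = 0 would give 84.1% with 25 and 89.7% with 30.

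With 25 completers and SD 1.3, two-sided 80% needs SDd of at most 1.712. That means 1 − r ≤ 1.712² / (2 × 1.3²) = 2.93 / 3.38 = 0.87, so r must be at least about 0.13.

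**6. Two readings that fit part of the text**

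- 25 raised to 30 per sequence: 60 in total and 15 in each of four groups. This matches the Summary's 60 but not the 30 in total of 4.3.3.
- 25 raised to 30 in total: this matches the 30 but not the words about each sequence, the 60 or the four equal groups.

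Both imply the same dropout allowance, 5/30 = 10/60 = 16.7%, so the unstated dropout rate does not decide between them.

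**7. Source of SD 0.5**

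The reference list gives number 63 as a study of antioxidant supplementation in cystic fibrosis. The Rationale and the Safety section cite the high-fat challenge in asthma as reference 36.

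**The case against.** The strongest reply is that the power statement is correct. It is a lower bound, the analysis is paired, and 50 people exceed 80% under both SDs and any non-negative correlation. That stands.

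A reader might infer that the figure is wrong because a two-sample formula with SD 1.3 gives less than 80% at 25 per group. The documents do not support this: no parallel comparison of meals is planned, and the text never says that 1.3 was the SD used.

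A reader might also infer that the trial is underpowered at 30. That is not shown either. Thirty completers give 82% even at SD 1.3 and r = 0, and SD 0.5 gives near-certain power. Nor does the section claim power within any single group, so a shortfall there would not contradict it.

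Finally, 60 may be what was intended, since it equals both 30 per sequence and 15 in each of four groups. This is plausible, but 4.3.3 says 30 in total and the Summary also opens with 30. The text does not settle it.

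**Conclusion.** The contradiction in the counts and groups stands and is in the current text: 50 implied, 30 recruited as though it allowed for dropouts, 60 in the Summary, and two groups against four. The power calculation is not recoverable, because the SD used, the within-person correlation, the sidedness and the dropout rate are all missing. The reference for SD 0.5 does not match the study described.

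Power depends on which total is meant. At SD 1.3, r = 0 and a two-sided 5% test, it is 96.5% with 50 completers, 82% with 30 and 74% with 25. At SD 0.5 it is near 100% throughout. The correlation and sidedness are my assumptions. What has to be corrected is an unsettled enrolment target and a power statement attached to 50, a number that no section plans to recruit.

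**What to change.** 1. Choose one total that divides evenly over the four strata. The text fits 60 (30 per sequence, 15 per stratum), or about 30 in total moved to a multiple of four such as 28 or 32. The choice is the sponsor's.
2. Use that total in the Summary, the Resumo and section 4.3.3, and replace the two groups of 15 with the four-group allocation.
3. State the dropout rate and the expected number of completers. Restate the power for the meal comparison pooled over the groups at that number, using the within-person SD. If that SD is unknown, show a range of r for both 1.3 and 0.5, and say whether the test is two-sided.
4. Correct the citation for SD 0.5, or confirm which study it came from.

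The cost is rewording and a short recalculation, with no change to design or procedures. If the smaller total is kept, the stated power may fall below 80% at SD 1.3 with r near zero (74% with 25 completers), and the text should say so.
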